## 10. Study follow-up

Participants will be assessed at screening, baseline (Week 0), Week 2, and then at monthly intervals until the primary endpoint at 6 months (Month 1, Month 2, Month 3, Month 4, Month 5, and Month 6). If deemed necessary by the attending uveitis specialist or pulmonologist, visits outside this schedule will be possible while preserving blinding. The research manager will continue contacting participants for subsequent monthly visits beyond the primary endpoint at 6 months, though these visits are not mandatory. If a scheduled visit does not occur or if its results are missing, the value measured on the date closest to the target scheduled visit within a

window period of  $\pm 2$  weeks will be used. If the latest visit does not fall within the 6-month period ( $\pm 2$  weeks), the closest visit to this timeframe will be used.

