**Intervention:**

All included participants will receive immunosuppressants at the discretion of the attending uveitis specialists. There will be no restrictions on topical or local treatments throughout the entire follow-up period, including surgical interventions, if indicated.

- *Arm 1: ATT*

The full course of ATT will consist two months in the intensive phase, followed by seven months in the continuation phase (2RHZE/7RH).

- *Arm 2: Control group*

The treatment for the control group primarily involved immunosuppressants without ATT.

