**Nature and extent of the burden and risks associated with participation, benefit and group relatedness:**

Adverse events

Adverse events will be recorded during the trial. Baseline consultation and workup include assessment of potential adverse events risks. Participants will be closely monitored by the internal medicine department. Participants can withdraw their consent at any time during the trial.

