## **1.3. Hypothesis**

Patients that received initial treatment incorporating a full course of ATT in QFT-positive patients with uveitis of undetermined cause is achieving complete uveitis resolution at six months and reducing uveitis relapse during follow-up after the initial six months.

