|                           |                                                                                                                                                                                                                                                                                                                                                                                                                                                                                                                                                                                                                                                                                                                                                                                                                            |     |
|---------------------------|----------------------------------------------------------------------------------------------------------------------------------------------------------------------------------------------------------------------------------------------------------------------------------------------------------------------------------------------------------------------------------------------------------------------------------------------------------------------------------------------------------------------------------------------------------------------------------------------------------------------------------------------------------------------------------------------------------------------------------------------------------------------------------------------------------------------------|-----|
|                           | Continuation phase: 3 times/week.
Duration: 9 months (2 months of FDC intensive phase + 7 months of FDC continuation phase). The duration will be standardized for all included participants, with exceptions for those requiring ATT adjustments due to other factors (e.g., adverse effects, allergies, etc.).                                                                                                                                                                                                                                                                                                                                                                                                                                                                                                        |     |

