## 9. Study analysis population

### c. The intention-to-treat (ITT) approach

All analyses will be first conducted using the ITT approach. The ITT population will include all participants who underwent randomization, regardless of any treatment switching that occurred. For participants who missed the six-month visit ( $\pm 28$  days), if any, last observation carried forward (LOCF) imputation will be performed..

d. The per-protocol approach

The per-protocol population will include all participants who were randomized, excluding those who do not have six-month visits or deviated from the treatment protocols (e.g., non-compliant, experience severe adverse effect, etc). If any, participants who switch treatment will also be excluded in this per-protocol analysis.

For patients receiving ATT, missing 2 weeks of medication will be considered non-compliance (protocol deviation). The pulmonologist will record the prescribed ATT and count the remaining drugs (i.e., ATT) at each visit to determine treatment non-compliance. For participants receiving systemic immunosuppressants, missing more than 1 week of the prescribed regimen will be considered non-compliance. Topical immunosuppressants will not be taken into account when determining compliance.

e. Additional approach for potential switching

In order to anticipate treatment switch, adjustment will be performed, particularly to analyze the secondary outcomes. Participants grouping will be subdivided into those receiving combination treatment besides the initial group of ATT alone and non-ATT. Specifically, participants that switch from non-ATT group to ATT will be classified as ATT in this adjusted analysis. Analysis following adjustment for switching treatment was performed with recalculation of the six-month follow-up time based on the actual treatment received, beginning from the start of their actual treatment.

However, results from the ITT analysis (without adjustment for switching) is considered to be more appropriate to evaluate the primary outcome, given that the purpose of the study was to compare the two strategies according to the treatment received at the time of randomization.

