## **11. Safety**

Adverse events will be recorded from all enrolled participants who had received at least one dose of study treatment (exposed) of any drug. Safety analyses will be based on the treatment regimen.

The safety analysis will be based on reported adverse events (AEs) in the case report forms, as well as any other identifiable information from each clinic visit, including those at the uveitis clinic or internal medicine/pulmonology clinic. This will also include data from medical records or laboratory values for each participant during the trial period.

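### The standard ATT course lasts 9 months but required visits end at Month 6, so adverse-event and adherence data for its last third depend on voluntary attendance

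*Supplement*

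**What the plan says.** **Length of ATT.** The treatment-arms table in SAP v2.0 section 3 gives "Duration: 9 months (2 months of FDC intensive phase + 7 months of FDC continuation phase". The Intervention paragraph of the final protocol's summary agrees: "two months in the intensive phase, followed by seven months in the continuation phase (2RHZE/7RH". The table adds: "The duration will be standardized for all included participants, with exceptions for those requiring ATT adjustments due to other factors".

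**Visits.** SAP section 10 lists screening, baseline, Week 2 and then monthly visits to Month 6. Of the period after that it says: "The research manager will continue contacting participants for subsequent monthly visits beyond the primary endpoint at 6 months, though these visits are not mandatory". Extra visits can take place when the uveitis specialist or pulmonologist thinks them necessary.

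**Adherence.** Under SAP section 9d the pulmonologist is to "count the remaining drugs (i.e., ATT) at each visit to determine treatment non-compliance". No other adherence measure is described.

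**Safety.** SAP section 11 draws on case report forms "as well as any other identifiable information from each clinic visit", naming the uveitis and the internal medicine/pulmonology clinics. It then adds medical records and laboratory values over the trial period. It does not say when that period ends for an individual participant. SAP section 14g reports the number and proportion of participants with any adverse event.

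**Related statements.** The protocol summary says: "Participants will be closely monitored by the internal medicine department". The hypothesis in protocol section 1.3 begins: "Patients that received initial treatment incorporating a full course of ATT". Protocol section 3 plans to close data collection in February 2024.

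**The concern.** The visit schedule follows the six-month primary endpoint, while the treatment runs three months longer. A participant on the standard course is still taking study drug in Months 7, 8 and 9, but nothing in the text requires anyone to ask about adverse events or count tablets in those months.

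Two results are exposed. The first is the adverse-event proportion in section 14g: those who attend voluntarily may differ from those who do not, so late events could be under-recorded, and selectively so. The second is treatment exposure: the hypothesis concerns a full course, but the last part of that course is documented only for those who come.

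**Working it through.** **Inputs**
- Course: 2 months intensive plus 7 months continuation (SAP section 3; protocol summary).
- Last required visit: Month 6 (SAP section 10).
- Frequency: once daily in the intensive phase, three times a week in the continuation phase (SAP section 3).
- Planned size: 39 to 40 per arm (SAP section 7).
- Planned closure: February 2024 (protocol section 3).

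**1. The plan's own duration.** 2 + 7 = 9 months, as stated.

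**2. Part of a standard course after the last required visit, with ATT started at randomisation.**
- Months: 9 − 6 = 3.
- Share of the course: 3/9 = 33%.
- Share of the continuation phase: 3/7 = 43%.
- Share of scheduled doses: in units of doses per week times months, the course is 2 × 7 + 7 × 3 = 35 and the last three months are 3 × 3 = 9, so 9/35 = 26%.

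**3. Ceiling on time.** With 40 ATT participants all completing 9 months, 40 × 3 = 120 of 40 × 9 = 360 patient-months. This measures time without a required assessment, not bias. Dropout (10% is anticipated) and adjusted courses would reduce it.

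**4. Effect on the section 14g proportion.** A participant with any event by Month 6 is already counted. Let *q* be the fraction still event-free at Month 6, *h* the fraction of those with a first event in Months 7 to 9, and *m* the fraction of those events not captured. The shortfall is *q* × *h* × *m*. The documents give none of the three, so the size cannot be stated. It can only lower the recorded proportion.

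**5. Controls who switch to ATT.** SAP section 9e anticipates switching and restarts the six-month clock at the start of actual treatment. Section 10 does not say whether required visits restart too. Assume a switch at month *s* and a full 9-month course.
- If visits do not restart, the share after Month 6 is (*s* + 9 − 6)/9 = (*s* + 3)/9: 4/9 = 44% at *s* = 1, 6/9 = 67% at *s* = 3, and 9/9 = 100% at *s* = 6.
- If visits do restart, the share is again 3/9 = 33%.

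**6. Closure date.** February 2024 less 9 months is May 2023. A 9-month course begun later than about that date would run past closure. The plan gives no last enrolment date, so this is a condition to check, not a demonstrated problem.

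**The case against.** The strongest reply is that an optional visit is not an absent one. Monthly contact continues after Month 6, unscheduled visits are possible, and the pulmonologist counts tablets at any visit that takes place. Medical records and laboratory values also feed the safety analysis. All of that stands, and it rules out some stronger readings that a reader might infer:

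- *That late events or stopped treatment leave no record.* SAP section 11 names sources that do not depend on scheduled trial visits. Capture may be incomplete; it is not nil.
- *That the schedule contradicts the promise of close monitoring.* That sentence gives no frequency and no end date, so both statements can be true. This is a gap in specification.
- *That every ATT course has this gap.* Courses adjusted for adverse effects or allergies are exempt from the standard duration.
- *That switchers necessarily have a longer gap.* This depends on the switch date, a full 9-month course and visits not restarting, none of which is stated.

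It is also fair that only first events in Months 7 to 9 can change the section 14g figure. The per-protocol set is tied to the six-month visit, and nothing shows that later tablet counts would alter a six-month comparison.

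What remains is that these routes are opportunistic. They narrow the gap without making assessment complete or equal between arms, and the plan does not say when adverse-event or adherence collection ends.

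**Conclusion.** The point holds as a mismatch between treatment duration and required follow-up. For a standard course started at randomisation, 3 of 9 months (33%) has no required adverse-event or adherence assessment. The adverse-event proportion in the ATT arm may be too low by an amount the documents do not allow one to calculate, and completion of the full course may be only partly verified.

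A reader might go further and infer that the main efficacy result is compromised. It is not: the primary endpoint is assessed at six months, within the required schedule.

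The conclusion assumes that the schedule in the SAP text is the whole schedule. A figure at the end of the protocol's Methods section is not reproduced in the text available for this review. If it shows required later visits, it would itself need reconciling with SAP section 10. The point merits correction, but it is an inexpensive improvement and does not threaten the trial's main conclusion.

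**What to change.** Reconcile SAP sections 10 and 11 with the 9-month course.

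1. Make the research manager's planned monthly contact after Month 6 a required adverse-event and ATT-adherence query in both arms, so that events are sought equally and late switches are recorded. Use the telephone when the participant does not attend. Keep the tablet count for those who do attend, since it cannot be done by telephone.
2. State that adverse-event collection runs to the last ATT dose for anyone taking ATT, including participants who switch to it.
3. Check that the February 2024 closure date leaves room for this, given the last expected ATT start.
4. If collection after Month 6 stays voluntary, report adverse events separately to Month 6 and after it, with the number of participants assessed in each period.

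Clinical tests and management in those months remain with the investigators. The cost is an amended paragraph, some added contact time and slightly more burden on participants.

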## **11. Safety**

Adverse events will be recorded from all enrolled participants who had received at least one dose of study treatment (exposed) of any drug. Safety analyses will be based on the treatment regimen.

The safety analysis will be based on reported adverse events (AEs) in the case report forms, as well as any other identifiable information from each clinic visit, including those at the uveitis clinic or internal medicine/pulmonology clinic. This will also include data from medical records or laboratory values for each participant during the trial period.

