## **14. Data analysis**

- a. All data will be pseudo-anonymized. A separate dataset (in Excel) containing participant IDs will be protected. A separate dataset without direct participant IDs will be generated and analyzed using SPSS.
- b. Baseline characteristics will be summarized according to trial group for the ITT populations.
- c. The primary outcome analysis will be focused on the proportion of complete uveitis resolution and the corresponding relative risk between the ATT and control groups. Cox proportional-hazards models will be used to estimate any uveitis resolution between the ATT and control groups. This analysis will be performed at the patient level, where resolution of uveitis is considered when both eyes meet the prespecified criteria. In bilateral

uveitis cases, if one eye shows uveitis resolution but the other does not, as prespecified in the previous section, these participants will be considered to have “no uveitis resolution”.

- d. Pairwise comparisons across experimental arms will be done using a Chi-square test or Fisher’s exact test as appropriate at the 5% significance level for the efficacy endpoint of uveitis resolution at six month time point (see above section). Relative risk will be calculated and presented with 95% confidence interval in the ITT and per-protocol analysis approaches.
- e. Time-to-uveitis resolution will be analyzed using the Cox proportional hazards model and hazard ratio.
- f. For uveitis relapse outcomes, the analysis will include participants with complete uveitis resolution, regardless of follow-up duration. Cox proportional hazards models, along with hazard ratio and Kaplan–Meier estimates, will be used for the analysis.
- g. The number (proportion) of participants experiencing any adverse events will be reported.
- h. Eye-level outcomes will be calculated based on the involved eyes for the presenting uveitis. Therefore, bilateral uveitis presentations will be counted as two eyes.
- i. A *p*-value of less than 0.05 will be considered statistically significant.
- j. All statistical analyses will be performed using IBM SPSS Statistics version 28.0.1.0 (142) for Windows (SPSS Inc.).

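### The only planned safety summary, a crude proportion with any adverse event by an undefined treatment regimen and without a per-participant window, can mix unequal observation and misplace events that precede a switch to ATT

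*Supplement*

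**What the plan says.** Four parts of SAP v2.0 bear on this.

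- **Population and grouping (section 11).** "Adverse events will be recorded from all enrolled participants who had received at least one dose of study treatment (exposed) of any drug". The grouping is then: "Safety analyses will be based on the treatment regimen". Regimen is not defined as assigned or received.
- **Period (section 11).** Events come from case report forms and from uveitis and internal medicine or pulmonology visits. In addition: "This will also include data from medical records or laboratory values for each participant during the trial period". No start, end or post-treatment window is set for the individual participant.
- **Measure (section 14g).** "The number (proportion) of participants experiencing any adverse events will be reported". No rate, time to event, or split by seriousness is given.
- **Follow-up and switching (sections 3, 9e and 10).** Visits run "at monthly intervals until the primary endpoint at 6 months" in both arms. Participants are then contacted for further monthly visits, "though these visits are not mandatory". The ATT course lasts 9 months. Section 9e anticipates switching: "participants that switch from non-ATT group to ATT will be classified as ATT in this adjusted analysis".

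The final protocol's summary adds only that events are recorded during the trial and that the internal medicine department monitors participants closely.

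**The concern.** A crude proportion with any event rises with time observed, so it compares groups fairly only if they are watched for similar periods. The plan secures that up to Month 6 and not beyond. ATT recipients are still taking trial medication in Months 7 to 9, and section 9d has the pulmonologist counting remaining drug at each visit. That may keep them in closer contact than controls.

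The second problem is attribution. A control may have an adverse event and later start ATT. Nothing in sections 11 or 14g ties the event to the treatment being taken at onset. If participants are grouped by treatment received, the event can move with the participant into the ATT column.

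The trial sets the toxicity of adding ATT against the risk of withholding it. With about 40 participants per arm, a few misplaced events can change how the safety table reads.

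**Working it through.** **The plan's own figures.** The safety sections state no number to reproduce. The one figure used here is the planned size in section 7, which does reproduce. With P = (0.44 + 0.14)/2 = 0.29,

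n = [(1.96√(2 × 0.29 × 0.71) + 0.84√(0.44 × 0.56 + 0.14 × 0.86)) / 0.30]² = 34.67, so 35 per arm,

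and 35/0.9 gives 39, stated as 39–40. I use 40 per arm. The documents give no adverse event rate and no switch count, so those inputs below are assumptions.

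**Check 1: unequal observation with no true difference.** Let h be the same monthly risk of a first event in both groups. The proportion with any event by month t is 1 − (1 − h)^t. The upper case has every ATT participant observed to Month 9 and every control only to Month 6. A milder case has half the controls also observed to Month 9, so the control proportion is the mean of the 6- and 9-month values.

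| h per month (assumed) | By Month 6 | By Month 9 | Ratio, all controls stop at 6 | Ratio, half stop at 6 |
|---|---|---|---|---|
| 2% | 11.4% | 16.6% | 1.46 | 16.6/14.0 = 1.19 |
| 5% | 26.5% | 37.0% | 1.40 | 37.0/31.7 = 1.17 |
| 10% | 46.9% | 61.3% | 1.31 | 61.3/54.1 = 1.13 |

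With a common window to Month 6 the ratio is 1.00 in every row.

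**Check 2: attribution of pre-switch events.** Take 40 per arm and an equal 20% risk, so 8 participants with an event in each arm. Let k controls have an event before ATT, then start ATT and be counted wholly as ATT. The ATT proportion becomes (8 + k)/(40 + k) and the control proportion (8 − k)/(40 − k).

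| k (assumed) | By randomised arm, ATT v control | By treatment received, ATT v control |
|---|---|---|
| 2 | 20% v 20% | 10/42 = 23.8% v 6/38 = 15.8% |
| 4 | 20% v 20% | 12/44 = 27.3% v 4/36 = 11.1% |
| 6 | 20% v 20% | 14/46 = 30.4% v 2/34 = 5.9% |

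For a rarer event, suppose 3 of 40 controls have a serious TB-related event and then start ATT, with none in the ATT arm. By randomised arm this is 0/40 on ATT v 3/40 (7.5%) on control. By treatment received it is 3/43 (7.0%) v 0/37.

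**Check 3: does section 9e's restarted clock remove the problem?** Section 9e also restarts a switcher's six-month follow-up at the start of the actual treatment. If that were carried over to safety, a pre-switch event would fall before the clock starts. Suppose it were then dropped and the switcher had no later event. At k = 2 the table would read 8/42 = 19.0% v 6/38 = 15.8%, and at k = 6 it would read 8/46 = 17.4% v 2/34 = 5.9%. The ATT column is no longer inflated, but the controls' events have disappeared.

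**The case against.** A reader might infer that the plan does compare the arms over unequal periods and does charge controls' harms to ATT. The documents do not support either statement as fact.

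- **Observation.** Section 10 contacts all participants for monthly visits after Month 6, without distinction by arm, and relapse beyond six months is an endpoint for both. Nothing fixes observation at 9 months on ATT and 6 on control. The protocol also gives a planned end of data collection (February 2024).
- **Grouping.** Section 11 does not say regimen received. Where the SAP means actual treatment elsewhere (sections 9e and 13), it says so. Section 9c puts ITT first for all analyses, which could be read as requiring a by-arm safety table first.
- **Switching.** Section 9e is aimed particularly at the secondary outcomes and does not name safety. It restarts the clock and mentions a combination-treatment subdivision, so a plain two-column merge does not follow from it.
- **Comparison.** Section 14g reports proportions and plans no formal test of adverse events.

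All of this stands as a limit on the claim, but it does not close the gap. Section 11 sets a population defined by exposure, which differs from the ITT population of section 9c, so it is unclear which rule governs. A by-arm analysis would settle attribution but still supply no window. A calendar end of data collection is not an individual risk period. Proportions printed by group will be read as a comparison whether or not a test accompanies them.

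**Conclusion.** The point holds as a risk left open by the wording. The only safety measure is a crude proportion, its grouping is undefined, it has no per-participant window, and no rule covers events before an anticipated switch. It can therefore compare groups over unequal observation and, if regimen is read as treatment received, place a control's pre-switch event under ATT.

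The sizes are illustrative. The ratio of 1.31 to 1.46 assumes equal constant monthly risks of 10% to 2% and the extreme attendance pattern. If half the controls stay to Month 9 it falls to 1.13 to 1.19, and it is 1.00 if attendance is equal. The shift from 20% v 20% to between 23.8% v 15.8% and 30.4% v 5.9% assumes two to six switchers who had an event before the switch and are counted whole as ATT. How large either effect would be in this trial cannot be derived from the documents.

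**What to change.** In sections 11 and 14g, replace the single proportion with two tables and define the grouping of each.

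1. **Randomisation to Month 6, by randomised arm.** Report the number and proportion of participants with an adverse event with onset in that period, which is covered by scheduled visits common to both arms.
2. **Whole follow-up, by treatment being taken at onset.** Assign each event to the treatment in use when it began, with patient-months on that treatment as the denominator. A switcher contributes control time before the switch and ATT time after it, and ATT Months 7 to 9 are covered.

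Neither table needs to be labelled the sole main comparison. Separate rows for serious events and incident active TB would be a useful but optional addition.

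The cost is SAP wording, one extra table, and the need for event onset dates and drug start dates, which should be obtainable from the records the SAP already draws on. The first table omits late ATT events, which the second shows. No treatment or visit changes.
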